**Figure 2 nutrients-16-00338-f002:**
[figure not shown]
Intervention outline.

**Table 1 nutrients-16-00338-t001:** Competency-based intervention: Zeliakide description.

Competence	Learning Outcome	Activity	Topic Day
The student should be able to place the food groups in the food pyramid.	*Bloom level 3. Application* The student adequately organises different foods in the pyramid.	Game about the food pyramid.	Day 1. Food groups Day 2. Healthy diet
The student should be able to identify dietary errors and make recommendations for its modification.	*Bloom level 4. Analysis* The student identifies foods to be consumed infrequently. *Bloom level 6. Evaluation* The student offers recommendations to adapt its consumption.	Complete and adapt a 24 h recall.	Day 1. Food groups Day 2. Healthy diet
The student should be able to consume less food from the top of the pyramid.	*Bloom level 6. Evaluation* Students consume less unhealthy food than before the activities.	Game about the food pyramid. Complete and adapt a 24 h recall. Healthy snacks challenge.	Days 2 to 8. Healthy snacks challenge. Day 2. Healthy diet (transversally)
The student should be able to explain what celiac disease is.	*Bloom level 2. Understanding* The student acknowledges that gluten harms people with celiac disease and makes them sick. The student concludes that people with CD should follow a gluten-free diet.	Game to learn the characteristics of the disease.	Day 3. Celiac Disease
The student should be able to analyse gluten	*Bloom level 3. Application* The student manipulates gluten and finds it. The student figures out that gluten gives elasticity to the doughs. *Bloom level 4. Analysis* Students deduce where gluten is by analysing food labels.	Experiment 1: Learning by doing: pasta made with different types of flour. Experiment 2: Food analysis through the senses.	Day 4. What gluten is Day 5. Where gluten is (transversally)
The student should be able to classify food groups according to gluten content.	*Bloom level 4. Analysis* The student identifies the food groups that contain gluten: placing them in cereals. The student concludes that processed foods may contain gluten.	Experiment 3: Gluten detection experiment, immunochromatography. Experiment 4: Study of food labelling.	Day 6. Food labels Day 7.Where gluten is Day 4. What gluten is (transversally)
The student should be able to understand the work of scientists, to know that the gluten content of foods is analysed through experimentation.	*Bloom level 6. Evaluation* The student is able to perform experimental work, observe, analyse and evaluate the results.	All the experiments.	Day 4. What gluten is Day 5. Differences between gluten and gluten free foods Day 6. Food labels Day 7. Where gluten is
The student should be able to assess the impact of own actions on others.	*Bloom level 6. Evaluation* The student demonstrates empathetic behaviour. The student selects actions and behaviours to overcome differences between people.	Game to learn the characteristics of the disease. Case study to work on inclusion: discussion.	Day 8. Social inclusion of people with celiac disease Day 3. Celiac Disease (transversally) Day 5. Differences between gluten and gluten free foods (transversally)

Meaning of “transversally”: some activities or days, in addition to developing their specific competencies and learning outcomes, contribute in a transversal way in the achievement of others. Thus, “transversal” has been used to indicate this situation.

**Table 2 nutrients-16-00338-t002:** Zeliakide intervention study schedule.

Intervention Group				Control Group
**Week**	**Topic Session 1**	**Topic Session 2**	**Challenge**	No intervention
1	Day 1. Food groups	Day 2. Healthy diet	“Healthy snacks challenge”	
2	Day 3. Celiac Disease	Day 4. What gluten is		
3	Day 5. Differences between gluten containing and gluten free foods	Day 6. Food labels		
4	Day 7. Where gluten is	Day 8. Social inclusion of people with celiac disease		

**Table 3 nutrients-16-00338-t003:** Competency-based intervention: outcome measures.

Competence	Outcome Measures
The student should be able to place the food groups in the food pyramid.	Change in nutrition knowledge
The student should be able to identify dietary errors and make recommendations for modification.	Change in nutrition knowledge
The student should be able to consume less food from the top of the pyramid.	Change in behaviour in relation to the consumption of unhealthy foods
The student should be able to explain what celiac disease is.	Change in Celiac Disease knowledge
The student is able to assess the impact of their own actions on others.	Change in intentional behaviour related to the social inclusion of people with celiac condition: perception of the influence of one’s own actions on others.
The student should be able to analyse gluten	Change in knowledge regarding gluten and its presence in foods
The student should be able to classify food groups according to gluten content.	Change in knowledge regarding gluten and its presence in foods
The student should be able to understand the work of scientists, to know that the gluten content of foods is analysed through experimentation.	Change in attitude in relation to interest in science

## Data Availability

Data are contained within the article and Supplementary Materials.

## Appendix A

**Table A1 nutrients-16-00338-t0A1:** Questionnaire to be completed by children to evaluate the intervention.

Competence	Question		Response
1	Do you know which foods are found in the different parts of the food pyramid?		Yes/No/No response
	Which foods are at the top of the pyramid?		Open question
	Which foods are at the bottom of the pyramid?		Open question
	Of the food pairs below, which do you think is highest in the food pyramid?		Tomato/Sweet, Pizza/Rice, Bread/Juice, Olive oil/Red meat, Potato/Ham
2	Of the foods you eat during the day, do you know which are unhealthy?		Yes/No
	Which are the unhealthy foods you eat?		Open question
	Are the foods that are often featured in advertisements usually healthy?		Yes/No/There is a bit of everything
	How much fruit and vegetables should you eat per day?		Open question
	What do you think you should improve your diet, for example, by eating more fruit, less sweets?		Open question
3	How many days a week do you usually take a healthy lunch to school (fruit, dairy products, wholemeal bread…)?		Scale 0 days–5 days
	Of the foods at the top of the food pyramid, how many do you eat at the weekend?		I eat them on Fridays, Saturdays and Sundays, more than once a day. I eat them on Fridays, Saturdays and Sundays, once a day. I only eat them one day at the weekend. I don’t eat them every weekend, only once in a while.
	Do you think it is important to eat a healthy diet?		No, if you do sport it is enough Yes, it is important but it is better for everyone to eat what they want Yes, it is very important for me.
	With what you have learned in these sessions, do you think you are able to improve your diet?		Yes, I know what mistakes I make in my diet and I am able to improve it Yes, I have learned a lot but I am not able to improve my diet No, I have not learned enough
	In the last month, have you eaten more, less or the same amount of the following food groups? (dairy products, fruits, vegetables, meat, fish, pulses, cereals, sweets)		Less/Equal/More/I do not know/No response
4	How much do you know about CD?		Scale 0 (nothing)–4 (much)
	What symptoms do people with CD have?		Open question
	When do people with CD develop symptoms?		Open question
	What compound in food is harmful to people with CD?		Open question
5	How do you think people with CD feel?		Open question
	Does a person with CD enjoy eating?		Scale 0 (nothing)–4 (much)
	What would you do if it was your birthday and a classmate had CD?		Bring the cake that I like the most. Bring the cake that I like the most and another gluten-free cake for the person with CD. Bring a gluten-free cake for everyone. No response.
6	Where is the gluten?		Open question
	What makes a dough elastic?		Gluten Water I do not know
	How can we know (without experimenting) whether a food contains gluten or not?		Open question
	Which symbols indicate that a food does not contain gluten?		Open question
7	Which of the following foods a person with CD cannot eat?		Meat and fish Eggs and dairy Fruit and vegetables Wheat-based products: biscuits, bread and pasta Rice and maize Sweets They can eat anything I do not know
	From the following list of foods, which ones may contain gluten?		Raw rice, raw beans, fresh fruits, fresh vegetables, natural dairy products, fresh meat or fish, biscuits, some sweets, sweetened cocoa powder, some ice-creams, chocolate
	Can a prepared food (cream of vegetables, prepared beans…) have gluten, even if it is made from gluten-free ingredients?		Yes/No
8	Please rate these sentences according to your level of agreement.	In order to detect gluten, laboratory experiments must be carried out.	Scale 1 (not agree)–5 (very agree)
		It is important for scientists to do experiments.	Scale 1 (not agree)–5 (very agree)
		In the future I would like to become a scientist.	Scale 1 (not agree)–5 (very agree)
		Researchers are crazy, weird and male.	Scale 1 (not agree)–5 (very agree)

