The intervention includes activities aimed at encouraging attitudinal and behavioural change related to healthy diet beyond the classroom. Among them, the most important is the “healthy snacks challenge”. This challenge aims to promote healthy mid-morning snacking among pupils. To this end, in the second session of the intervention, students will be divided into groups. Every day (during the month of the intervention), the children will write down their mid-morning snack in a specific section of a workbook. On the last day of each week, the people who are part of the research team will be in charge of giving the corresponding scores for the snacks. Healthy snack, 1 point (fruit, natural dairy products, dried fruit, vegetables, etc.); medium-healthy lunch, 0.5 points (in addition to the aforementioned foods, it includes some unhealthy food); and unhealthy lunch, 0 points (industrial pastries, biscuits, milkshakes or industrial juices, etc.). 

As mentioned above, the children will compete in groups. In this way, collaborative work will be encouraged, where everyone must strive to achieve a common goal. Likewise, every day, they will address the concept of a healthy diet. 

The necessary material for the Zeliakide program has been already designed. A teaching unit has been produced that includes the following material: a notebook containing the contents of the intervention, a virtual classroom where participants can view the contents of each day and interact with the researchers, and the material to carry out the proposed experiments and games (worksheets, power points, laboratory equipment, online games). In order to provide innovative digital material to the classrooms, an augmented reality application that contains all the information in the notebook has also been designed. Through this application, students will be guided by an avatar, a virtual researcher, who will help them carry out the experiments.

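### The competence 3 school-snack item does not match the programme's own snack classification: children decide whether milkshake and mixed-snack days count as healthy, and the teaching may change that decision in one group only

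*Protocol article*

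**What the plan says.** Section 2.5.1 presents the snack challenge as the leading activity for changing behaviour outside the classroom: "This challenge aims to promote healthy mid-morning snacking among pupils". Researchers score the snacks that children record each day at three levels:

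- The top level is defined as "Healthy snack, 1 point (fruit, natural dairy products, dried fruit, vegetables, etc".
- A mixed snack falls in the middle level, "medium-healthy lunch, 0.5 points (in addition to the aforementioned foods, it includes some unhealthy food".
- The bottom level is defined as "unhealthy lunch, 0 points (industrial pastries, biscuits, milkshakes or industrial juices, etc".

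The questionnaire in Appendix A, Table A1, asks about the same behaviour under competence 3: "How many days a week do you usually take a healthy lunch to school". The examples given there are fruit, dairy products and wholemeal bread. The list of examples is left open, and the answer is a bare count, "Scale 0 days–5 days".

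In Table 3, competence 3 feeds the outcome "Change in behaviour in relation to the consumption of unhealthy foods", and section 2.6.1 makes the Table 3 outcomes primary, measured by the children's questionnaire. The challenge points are not listed as an outcome. According to Table 2 and section 2.5.2, the control group receives no intervention and continues with the normal curriculum.

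**The concern.** The item and the programme describe a healthy school snack differently. The programme limits dairy to natural products and puts milkshakes in the lowest category. The item names dairy products without a qualifier and excludes nothing. The programme has a middle category for mixed snacks, whereas in the item each day either counts or does not, with no rule for a mixed day.

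Two consequences follow. First, a child who improves in the way the programme trains may give the same count before and after. Second, and more serious for a controlled comparison, children in the intervention group learn the programme's classification between the two measurements and controls do not. If taught children become stricter about what counts, their reported days can stay flat or fall while their snacks stay the same or improve. That is a change in how the question is understood, in one group only, and it enters the between-group difference as bias. Later coding cannot undo it, because the count does not record which foods were taken.

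**Working it through.** The plan states no figure on this point, so there is nothing to reproduce. The check compares the two classifications and then follows some example weeks through both.

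**1. Side by side** (section 2.5.1 against Table A1)

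| Snack | Challenge score | Item |
|---|---|---|
| Fruit | 1 | named as healthy |
| Natural dairy | 1 | covered by dairy products |
| Milkshake | 0 | not excluded; left to the child |
| Healthy food plus some unhealthy food | 0.5 | no rule; left to the child |
| Wholemeal bread | not named | named as healthy |

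**2. A child who improves and keeps one reading throughout.** The child replaces a milkshake by fruit on 2 days and a mixed snack by a fully healthy one on 2 days. The fifth day does not change.

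Challenge gain = 2 × (1 − 0) + 2 × (1 − 0.5) = 3 points per week.

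The item's change over those 4 days depends on the reading:

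| Milkshake counted as healthy? | Mixed snack counted as healthy? | Before | After | Change |
|---|---|---|---|---|
| yes | yes | 4 | 4 | 0 |
| yes | no | 2 | 4 | 2 |
| no | yes | 2 | 4 | 2 |
| no | no | 0 | 4 | 4 |

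The same improvement is recorded as anything from 0 to 4 days.

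**3. A child whose reading changes.** Suppose the child counts both kinds of day at pre-test and neither at post-test.

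- Snacks unchanged, with 2 milkshake days and 2 mixed days: the challenge score changes by 0, and the item goes from 4 to 0, a change of −4.
- Milkshakes replaced by fruit on 2 days, mixed snacks kept on 2 days: the challenge score rises by 2 × (1 − 0) = 2, and the item goes from 4 to 2, a change of −2.

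If a fraction f of the intervention group recounts k days each in this way and controls do not, the between-group difference in mean change shifts by f × k days. The documents give neither f nor k. In the example week k can reach 4.

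**4. All possible weeks under a fixed reading.** Five days split into healthy, mixed and unhealthy give 21 possible weeks, and 197 ordered pairs of weeks in which the challenge score rises. Across these pairs the item rises in 151 (77%), is unchanged in 35 (18%) and falls in 11 (6%); the percentages are rounded. The counts are the same whether mixed days are read as healthy or not. For example, going from five unhealthy snacks to five mixed ones raises the score from 0 to 2.5, while the item stays at 0 if mixed days are not counted. These are shares of possible patterns, not frequencies to expect in the trial. They also treat every unhealthy day as reported unhealthy, so the milkshake ambiguity comes on top.

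**The case against.** The strongest reply is that the item asks about a healthy lunch and only illustrates the word with examples. Nothing in it says that a milkshake counts. That is right. A reader might infer that the item accepts any dairy product and so contradicts the programme outright, but the open-ended list supports only ambiguity.

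Second, the challenge points are a classroom device and not an outcome, and a day count need not mirror them. This also stands: no outcome is scored in two conflicting ways. It does not answer the concern that the teaching changes how one group reads the question.

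Third, competence 3 has five items. The last-month food-group item can register more fruit or fewer sweets, and the weekend item covers foods from the top of the pyramid. A reader might infer that the primary behaviour outcome misses the effect of the challenge altogether, and the documents do not support that. These items recover only part, however. Neither counts school-snack days, and the food-group item treats dairy as one group, so a switch from milkshakes to natural dairy escapes it too.

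Fourth, the word lunch in the item might be taken for a different meal from the mid-morning snack. Section 2.5.1 uses lunch for that same snack in its scoring, so this difference carries no weight.

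Finally, children are helped to understand the questions. Section 2.5.2 assigns that help to researchers and the teacher in the intervention group at pre- and post-test, and to the teachers alone in the control group. It does not guarantee one reading across groups.

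**Conclusion.** The mismatch is in the text and affects one item feeding a primary behaviour outcome. It makes that item ambiguous; it does not make the trained change unrecordable, since most improving patterns still move the count. In the example child, a gain of 3 challenge points is recorded as 0 to 4 days, depending on whether milkshakes and mixed snacks are counted.

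The possible bias between groups rests on one assumption: that some intervention children apply the taught classification at post-test and did not at pre-test. The documents do not say how many would. The bias runs against the programme if teaching makes children stricter, but the documents do not settle its direction. The point is moderate in weight and cheap to resolve before data collection.

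**What to change.** Reconcile the item's food examples with the challenge scoring, in particular the dairy wording and whether wholemeal bread belongs in both lists. Then state in the item how a day with a mixed snack is counted, with identical wording for both groups and all time points. There are two ways to do so:

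- say that a day counts only if the whole snack is healthy; or
- ask for three counts of school days: only healthy foods, mixed, and only unhealthy foods.

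The three counts also record a move from an unhealthy to a mixed snack (0 to 0.5). Two counts (only healthy foods; any unhealthy food) would not, because mixed and wholly unhealthy snacks both fall in the second.

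The intervention need not change. The cost is slightly more answering time, and the printed examples show a little of the taught classification to children at pre-test and in the control group.

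### The weekend unhealthy-eating item names no foods and relies on a term the programme teaches, so its answers can change without any change in eating

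*Protocol article*

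**What the plan says.** Table 3 lists "Change in behaviour in relation to the consumption of unhealthy foods" among the primary outcomes, and Section 2.6.1 says these are measured by the children's questionnaire. In Table A1 the outcome is covered by the five items under competence 3. The weekend item reads "Of the foods at the top of the food pyramid, how many do you eat at the weekend". It offers four ordered frequency categories and no list of foods.

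Under competence 1 the same questionnaire asks "Do you know which foods are found in the different parts of the food pyramid", with No as a permitted answer, and then "Which foods are at the top of the pyramid" as an open question. Table 3 treats this as a separate primary outcome, change in nutrition knowledge. Table 1 gives the matching learning outcome, "The student adequately organises different foods in the pyramid", and assigns it to Days 1 and 2.

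Section 2.5.2 says that, in the intervention arm, the part of the questionnaire belonging to a session is answered at its start and again at its end. The post-questionnaire is repeated one month after the intervention. Controls keep their normal curriculum and complete the questionnaire in one sitting.

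**The concern.** The behaviour item can be answered as intended only by a child who already has the knowledge that the programme sets out to give. When that knowledge changes, so does the question the child is answering, even though the printed words stay the same. The reported frequency then mixes two things: how often the child eats certain foods, and which foods the child places in the category.

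The programme acts on the second of these mainly in one arm. A between-group comparison therefore cannot subtract it. What is at stake is how one component of a primary outcome is read: a change in the item could be taken as changed intake when it partly reflects the knowledge outcome.

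**Working it through.** No figure in the article is in dispute. The check sets the sections side by side and then gives a scale.

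**1. Does the item depend on taught knowledge?** Yes. It names no foods (Table A1, competence 3). Table A1, competence 1 allows that a child may not know them. Table 1 teaches them on Days 1 and 2.

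**2. Can the answer move with intake fixed?** Take a child who eats food X on one weekend day and food Y once a day from Friday to Sunday.
- If the child counts only X as top, the answer is one day at the weekend.
- If the child counts X and Y as top, the answer is once a day on all three days, one category worse.
- A child who wrongly counted Y as top and learns otherwise moves one category the other way.

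The pyramid itself is not shown, so X and Y are left unnamed.

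**3. Do the waves separate the two causes?**
- Sessions last one hour (Section 2.5.1). If the item is asked at the start and end of one session, no weekend falls between the answers, so a pre-post change cannot reflect changed weekend eating.
- Intake could have changed by one month, but the repeat uses the same wording and so carries the same shift.

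**4. Which other competence 3 items are affected?**
- The last-month food-group item names its groups, including sweets, and does not depend on the pyramid. It is a less/equal/more rating and not a frequency.
- The item "How many days a week do you usually take a healthy lunch to school" gives fruit, dairy and wholemeal bread as examples, which partly fixes its meaning. The challenge scoring in Section 2.5.1 is narrower on dairy and gives "unhealthy lunch, 0 points (industrial pastries, biscuits, milkshakes or industrial juices, etc", but its healthy list is also open-ended and includes foods the item does not name. The item is only weakly affected.

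**5. Scale (illustration only).** Let q be the net share of intervention children who move one category with no change in eating, with the categories scored 1 to 4. The spurious standardised difference is q/SD.
- Section 2.3 plans for d = 0.32. That figure is for knowledge and serves here only as a yardstick. Setting q/SD = 0.32 gives q = 0.32 × SD.
- The article gives no SD. Assumed values: SD 0.8 gives 0.32 × 0.8 = 0.256 (26%), SD 1.0 gives 32%, and SD 1.5 gives 48%.
- Assume 60 children per arm (the 120 in Section 2.3, split equally) and ignore clustering. The chance of p < 0.05 is then about Φ(q/SD × √(60/2) − 1.96). At SD 1.0, q = 20%, 30% and 50% give 0.19, 0.38 and 0.78. For q = 30%, the result runs from 0.54 (SD 0.8) to 0.19 (SD 1.5).

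These figures show what share of children would matter. They do not show what share would reclassify.

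**The case against.** Five points can be made for the plan.

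- **No evidence of reclassification.** The article has no data on how many children would change their reading of the term. This stands: one can say that answers can shift, not that they do.
- **Other items exist.** Competence 3 has five items and the article ranks none above the rest. The food-group item names foods. A reader might infer that the whole behaviour outcome rests on taught terms, and the documents do not support that.
- **Controls are not untaught.** Section 2.2 says that both school years work on diet in the curriculum, and the controls are the older year. A reader might infer that the shift occurs only in the intervention arm; mainly is as far as the text goes. Prior knowledge in controls does not remove the shift among taught children.
- **Baseline may already follow some teaching.** Table 1 ties competence 3 to Day 2 onwards, while the pyramid game is listed under Days 1 and 2. If the item is first asked on Day 2, some reinterpretation may precede the pre-measure. That would shrink the pre-post shift but would not make the item clear.
- **Adults help with wording.** Section 2.5.2 provides help in understanding the questions. This may reduce confusion, but no fixed food list is described, and the helpers are researchers and a teacher in one arm and teachers in the other.

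Nor is this something an analysis plan could put right later. The instrument is printed, and the frequency answer does not record which foods the child had in mind.

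**Conclusion.** The point holds for the weekend item, as a cheap improvement. The item feeds a primary behaviour outcome, leaves its foods unnamed, and depends on knowledge that is both taught and scored as another primary outcome. Neither the control arm nor the one-month repeat removes the resulting ambiguity.

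The size is unknown and the direction is not fixed. A reader might infer that the programme will look ineffective or harmful on behaviour because it succeeded on knowledge. That is one possible outcome: learning more top foods pushes reports that way, but learning that some foods do not belong there pushes them back. The conclusion about same-session timing rests on the assumption that this item follows the general rule in Section 2.5.2.

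**What to change.** Before the first wave, replace the reference to the top of the pyramid in the weekend item with a fixed list of named foods. Take the list from the programme's own pyramid and from its unhealthy-snack examples in Section 2.5.1. Keep the four existing response categories, and use identical words in both arms and at all waves.

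If the present wording is kept, state in advance that the item is supportive only and that a change in it will not be read as changed intake.

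The cost is the rewording of one item and the loss of comparability with any earlier data collected with the old wording. No new snack-recall instrument is needed for this point.

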### 2.6. Outcome Measures

#### 2.6.1. Primary Outcomes

Due to the fact that the present intervention is based on competencies and learning outcomes, the results are also proposed according to them, differentiating between knowledge-related results and those related to behaviour, which are more difficult to achieve. The primary outcomes are shown in Table 3. 

As mentioned, the primary outcomes will be measured by a pre- and a postquestionnaire reported by children at the beginning of the session, before the activities and discussion of the topic, and at the end of the session. They will be measured again one month after the intervention.

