### 2.8. Statistical Analysis

The description of the characteristics of the participants and data from the pre-, post- and retention test (one month after) questionnaires will be reported per group (control and intervention). 

For the analysis of the differences between groups, a variety of statistical tests will be used depending on the type of response to the questions (continuous, discrete or qualitative). Based on the distribution of the variables of interest in the sample, descriptive statistics for continuous data will be presented using the mean and standard deviation or the median and interquartile range. Qualitative data shall be presented as frequencies and percentages. Quantitative variables will be analysed using an ANOVA of repeated measures test using the group as a factor of the independent level (parametric) or Wilcoxon’s test segmenting by group (non-parametric). On the other hand, qualitative variables in two categories will be analysed with Chi-square and Cochran’s Q tests. Finally, qualitative variables in more than two categories will be analysed with Chi-square and McNemar Bowker’s tests.

Data will be entered and analysed using SPSS 28.0 software. A confidence interval of 95% and significance level of *p* < 0.05 will be assumed.

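### The weekend item on top-of-pyramid foods, one of five behind a primary behaviour outcome, has no answer for two days or for never, so some changes are misclassified or invisible

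*Protocol article*

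**What the plan says.** The item stands in Appendix A, Table A1, under competence 3. Its stem is "Of the foods at the top of the food pyramid, how many do you eat at the weekend". Four answers follow, from highest to lowest intake:

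- the highest: "I eat them on Fridays, Saturdays and Sundays, more than once a day"
- the next two, printed side by side: "I eat them on Fridays, Saturdays and Sundays, once a day. I only eat them one day at the weekend"
- the lowest, which describes occasional eating: "I don’t eat them every weekend, only once in a while"

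Competence 3 concerns eating less from the top of the pyramid. Table 1 gives its learning outcome as "Students consume less unhealthy food than before the activities", and Table 3 gives its outcome measure as "Change in behaviour in relation to the consumption of unhealthy foods". Section 2.6.1 makes that outcome primary: "The primary outcomes are shown in Table 3".

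Section 2.8 chooses the test by type of response. An item with several answer categories would fall under this rule: "qualitative variables in more than two categories will be analysed with Chi-square and McNemar Bowker’s tests". The article gives no coding rule for a child whose weekend fits none of the four answers.

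**The concern.** An item meant to detect lower intake needs an answer for every level a child can plausibly be at, before and after the programme. Here the weekend is defined as three days, yet the answers go from three days straight to one. The bottom answer describes occasional eating, so a child who never eats these foods has no answer either. Dropping one day out of three, or stopping altogether, are both plain ways to meet the learning outcome in Table 1.

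The stem also asks for an amount while the answers describe frequency. This is the lesser part of the point, because the gaps in the answers remain however the stem is worded.

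The gaps are fixed in the printed instrument. No later analysis plan can recover a category that the child was never offered.

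**Working it through.** No calculation applies, and there is no figure in the plan to reproduce. The check lists the possible weekend states and matches each to the printed answers, numbered 1 (highest intake) to 4 (lowest).

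| True state | Matching answer |
|---|---|
| Three days, more than once a day | 1 |
| Three days, once a day | 2 |
| Two days, any number of times | none; nearest are 2 and 3 |
| One day, any number of times | 3 |
| Not every weekend, occasional | 4 |
| Never | none; nearest is 4 |

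Four of the six states have a true answer and two do not.

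Next, what is recorded when a child's intake falls:

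| True change | Recorded as |
|---|---|
| Three days, from more than once to once a day | 1 to 2: correct |
| Three days more than once a day, to two days | 1 to 2 or 1 to 3: a decrease either way, at the wrong level |
| Three days once a day, to two days | 2 to 2 (no change) or 2 to 3 (a fall to one day) |
| Two days to one day | 2 to 3 (a decrease) or 3 to 3 (no change) |
| Occasional to never | 4 to 4: no change |

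If the item is analysed with the McNemar-Bowker test, that test compares opposite off-diagonal cells of the before-after table. A child recorded as 2 to 2 or 4 to 4 falls on the diagonal and adds nothing. A child recorded as 2 to 3 counts as a shift of one category in the right direction, although the label overstates the fall.

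Last, what the rest of competence 3 can pick up. It has five items. The school-lunch item uses a complete scale of 0 to 5 days. The last-month item asks for less, equal or more by food group, with sweets among the groups. Both can show change without the weekend item. Neither measures the same thing: the first counts days with a healthy lunch at school, and the second asks the child to judge change instead of reporting current frequency. The weekend item is the only one of the five that asks directly how often top-of-pyramid foods are eaten.

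**The case against.** The strongest case against is that this is a small wording fault in one item of five, and that its consequences are easily overstated. Most of that stands.

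- A reader might infer that a fall from three days to two cannot be recorded at all. The answers do not support this. A child who starts at answer 1 shows a decrease whichever neighbouring answer is chosen. Only a child who starts at answer 2 can appear unchanged.
- A reader might take three days to two as the smallest step that matters. Going from more than once to once a day on all three days is a smaller step, and answers 1 and 2 capture it.
- A reader might express the error in days. That assumes day scores, and the article assigns none.
- A reader might infer bias between the arms. Section 2.5.1 rewards healthy snacks in the intervention group, and Section 2.5.2 has researchers help those children before and after the intervention while teachers help the controls. Different rounding is therefore plausible. It is not shown, and the wish to report lower intake would affect a complete scale too.
- The mismatch in the stem may come from translation. The programme is built for Spanish schools, and the wording put to the children is not shown. Adults also help the children to understand the questions. This weakens the point about the stem. It does not supply the missing answers.

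What the objection does not remove is that two ordinary states have no true answer and no coding rule covers them.

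**Conclusion.** The point holds as a fault in one item. The four answers are not exhaustive: two days and never are missing. A change from three days once a day to two days is misclassified in one of two ways, and a change from occasional to never is invisible. This weakens one contribution to a primary behaviour outcome and does not invalidate that outcome.

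The size cannot be derived from the document. At each wave the share of children without a true answer equals the share at two days plus the share at never, and the article gives neither. The direction of any net error is also unknown, since it depends on how children round.

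The conclusion rests on two assumptions: that the printed answers match those given to the children, and that no separate instruction tells helpers how to place a child at two days or never.

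**What to change.** Before data collection, which the Discussion still places in the future:

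1. Keep the four ordered answers.
2. Add an answer for two days of the weekend, between the three-day and one-day answers, and an answer for never at the bottom.
3. State that the one-day and two-day answers apply whatever the number of times per day.
4. Reword the stem to ask how often.
5. Use the same version in both arms and at all waves.

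The resulting six answers cover every state in the first table. Replacing the item with a bare count of 0 to 3 days would be worse: it would merge occasional with never and lose a category that the item already has.

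The cost is rewording one question. Children have two more answers to read, and comparability with any pilot answers to this item is reduced.
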